#### Exclusion criteria

Patients who will meet any of the following criteria will be excluded:

(a) Comorbid tumor metastasis with other tissues and organs (liver, kidney, lung, brain, and others); (b) underlying severe heart disease, cerebrovascular disease, and mental illness; (c) patients with shoulder joint diseases and pathology before surgery; (d) negative SLNB result; and (e) unable to understand the rehabilitation training program provided by doctors and physiotherapists.

### Concealed randomization and blinding

Prior to the study, a computer-generated random sequence will be generated by an external researcher who is not otherwise affiliated with the study, and the sequence will be concealed in opaque envelopes. Group assignment will be disclosed to the executive doctor by telephone after study inclusion and participation in the familiarization period. Participants will be allocated using a 1:1:1:1 ratio to the A, B, C, and D groups.

The blinding to division results will be maintained by the study designer until the end of the study to ensure concealment of group allocation, and thus, the outcome assessor and the data analyst will also be blinded. The subjects and the therapists will be instructed not to disclose the allocation to the outcome assessor, and accidental unblinding will be documented.

### Assessment for training

After providing informed consent, participants will be asked standardized questions about their demographic characteristics and medical history. Clinical data will be extracted from the medical records regarding primary tumor, time of primary diagnosis, surgical operation, physical examination, laboratory testing, and imaging examination. To ensure the safety of the training, a therapist will evaluate the patient’s overall health, including physical function, physical activity, mental status, and PDV. Next, the training intensity will be adjusted before patients begin the training. The assessments will include upper limb mobility, grip, limb circumference, PDV, and pain.

Upper limb mobility is mainly reflected in both ROM and muscle strength. A medical protractor is usually used to assess the range of shoulder motion and follow standardized measurement principles to reduce compensatory motion. Passive flexion and abduction of the shoulder will be assessed in a supine position with gravity as a standard resistance. Active flexion and abduction will be assessed in a sitting position. Manual muscle test (MMT) and dynamometer are generally used to measure the maximum strength of the shoulder muscles. Strength evaluation will require the patients to take the supine position in the early stage and then gradually change to the sitting position in the late stage. The arms will be fixed at 90° to assess flexion and abduction muscle strength. The patient will be asked to perform three maximum voluntary contractions in each direction, recording the highest data from three attempts. Each arm will be measured separately. The most common method to determine whether the upper extremity has edema is the measurement of upper limb circumference. Using the antecubital fossa and palm as location points, the circumferences of the bilateral arms in a specific position will be measured, and the differences will be compared between the two sides. If the difference between the two sides is greater than 2 cm at the same site, it will indicate edema. PDV and pain will be assessed through consultation. PDV will be recorded by the nurse and will be uploaded to the hospital work system regularly. The therapist will ask the nurse about PDV and pain or directly search the system. Daily pain or pain at the end of the active/passive range of each exercise will be measured clinically using a standardized 10-cm visual analog scale (VAS). VAS is widely used clinically to assess postoperative pain and to monitor the effectiveness of treatment. VAS is based on self-reporting via a unidimensional scale that aims to represent subjective pain intensity [25, 26].

The six measurements will be tested at postoperative 1 day, 3 days, and 1 week, after which the patients will visit the hospital for evaluation once every other week. The ROM, muscle strength, and grip strength results will be used as criteria for maximum exercise intensity settings, and pain, PDV, and limb circumference will be used as indicators to assess whether exercise intensity is appropriate. Exercise intensity will set based on the current test results. If the evaluation index deteriorates, the intensity should be adjusted appropriately.

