#### Secondary parameters

Quality of life (QOL) is a multidimensional, subjective construct that reflects physical, mental, and social health domains of patients [32]. The European Organization Research and Treatment of Cancer (EORTC) QLQ-BR23 questionnaire is one of the most available tools for assessing aspects of QOL for BC patients [33]. It contains 23 items divided into two functional scales, including body image and sexuality, and three symptom scales, including arm symptoms, breast symptoms, and systemic therapy side effects. This questionnaire has been found to have a high internal consistency for 4 out of 5 scales and well-known group discriminative ability [34]. The validity of the EORTC QLQ-BR23 has been internationally scrutinized and explored in many countries, which has ultimately confirmed the questionnaire’s validity in BC [35].

The SF-36 is a general brief self-report questionnaire that assesses health-related QOL. The SF-36 contains 36 items that measure eight multi-item variables, including physical functioning, social functioning, role limitations due to physical problems, role limitations due to emotional problems, mental health, energy and vitality, bodily pain, and general perception of health, and there is a single-item scale on health transition. The score of each item ranges from 0 to 100. For each variable, the item scores are calculated, and a higher score indicates a better health status [36]. The internal consistency of the variables in the SF-36 is assessed with Cronbach’s α statistic and test-retest reliability [37]. Studies have shown that the SF-36 is acceptable for patients, and it has a high level of internal validity and good test-retest properties [38].

The assessments of shoulder function and quality of life will be evaluated at 1 week, 3 weeks, and 9 weeks after surgery.

In addition, joint mobility, muscle strength, grip, circumference, PDV, and pain, the parameters of exercise intensity in the pre-assessment, will also be evaluated as outcomes. Assessment methods and principles are the same as those for pre-assessments.

Shoulder ROM and strength will be assessed at postoperative 3 days and 1, 2, 3, 6, and 9 weeks. Grip will be evaluated at postoperative 1 day, 3 days, and 1, 2, 3, and 6 weeks, and upper limb circumference will be assessed at postoperative 1 day and 3, 12, and 18 weeks. PDV, pain, and skin will be evaluated by interview and palpation at postoperative 1 day, 3 days, 1 week, and 2 weeks.

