### Statistical analyses

Analyses will be performed using SPSS statistical software (version 20.0) by a statistician in the Department of Rehabilitation Medicine, Zhongnan Hospital of Wuhan University. Data will be analyzed according to the “intention-to-treat” (ITT) principle. A two-sided significance level of 5% will be used for all analyses. If the experimental data satisfies the normal distribution and the homogeneity of the variance, one-way analysis of variance (ANOVA) will be performed for comparison among the 4 groups with respect to the CMS, EORTC QLQ-BR23, SF-36, ROM, strength, grip, circumference, PDV, and pain. If there is an overall difference, the Tukey method for multiple comparisons will be used to compare the differences between groups at each time point. The results of repeated measurement ANOVA testing at each time point in each group will be analyzed by repeated measures to observe the recovery of patients at different times after surgery. For data with irregular variance, variable transformation can be used after the Kruskal-Wallis *H* test.

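### Shoulder strength is tested supine early and sitting later, so the planned recovery trend in strength mixes recovery with a change of test

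*Protocol article*

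**What the plan says.** Under Assessment for training, the protocol article names the instruments: "Manual muscle test (MMT) and dynamometer are generally used to measure the maximum strength of the shoulder muscles". For the strength test, patients are to "take the supine position in the early stage and then gradually change to the sitting position in the late stage". The arm angle is the same in either position: "The arms will be fixed at 90° to assess flexion and abduction muscle strength". No visit, week or criterion is attached to the change of position. The range-of-motion measures in the same section each have a single position: passive movement is measured supine, and for active movement "Active flexion and abduction will be assessed in a sitting position".

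The Secondary parameters section says that the pre-training measures, muscle strength among them, "will also be evaluated as outcomes", and adds: "Assessment methods and principles are the same as those for pre-assessments". The visits are also given: "Shoulder ROM and strength will be assessed at postoperative 3 days and 1, 2, 3, 6, and 9 weeks".

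Under Statistical analyses, strength is compared among the four groups by one-way ANOVA. If that shows a difference, "the Tukey method for multiple comparisons will be used to compare the differences between groups at each time point". A repeated-measures analysis within each group is then to be read as the course of recovery after surgery.

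**The concern.** A measure followed over time has to be the same measure at each visit. Here the load on the limb changes part of the way through the series, because the trunk position changes while the arm angle does not. A reading lower than the previous one may mean less strength or a harder test, and a rise may be understated. This bears directly on the repeated-measures analysis of strength.

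The comparison between groups is also exposed, but only under a condition. It is sound at any visit where all four groups are tested in the same position. A gradual change with no common visit does not ensure that. If patients who progress faster were seated sooner, their readings would be lowered relative to the others at that visit. A real benefit of earlier training could then be hidden, or a false difference created.

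**Working it through.** The plan gives no figure to reproduce, so the first two steps set the passages side by side. The last two are illustrations on assumed inputs.

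**1. Does the change of position reach the outcome?** Yes. Assessment for training prescribes the change, and Secondary parameters carries the same methods over to strength as an outcome at six visits from day 3 to week 9.

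**2. Does the fixed 90° angle equalise the load?** No.

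| Direction tested, arm at 90° | Supine | Sitting |
|---|---|---|
| Flexion | arm vertical; gravity has almost no moment | arm horizontal; full moment against the movement |
| Abduction | arm moves across gravity; almost no moment against the movement | arm horizontal; full moment against the movement |

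For the same muscle effort, an uncorrected dynamometer reads lower in sitting.

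**3. Size of the offset (assumed inputs).** Assume an upper-limb mass of 2 to 4 kg and a centre of mass half-way to the point where force is measured.

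- Offset δ = mass × 0.5 × 9.81 m/s².
- 2 × 0.5 × 9.81 = 9.8 N; 4 × 0.5 × 9.81 = 19.6 N.

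If a share p of a group is seated at a visit, the group mean there is lowered by δ × p. With everyone supine on day 3 (p = 0) and everyone seated at week 9 (p = 1), both assumed, the change from day 3 to week 9 is understated by the whole of δ. This holds even if all patients switch together. A gradual switch spreads the loss over several visits.

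**4. Between groups, if the seated share differs (assumed inputs).** The artefact is δ × dp, where dp is the difference in seated share. For dp = 0.2, 0.4 and 0.6 it is:

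- 9.8 N × dp = 2.0, 3.9 and 5.9 N;
- 19.6 N × dp = 3.9, 7.8 and 11.8 N.

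The article gives no standard deviation (SD) for strength, so these cannot be judged against the variability. In SD units, let sitting lower the reading by h SD, with two groups 20% seated and two groups 20% + dp seated, and no true difference. The noncentrality of the four-group F test is λ = n(h·dp)² / v, with v = 1 + h² × mean of p(1 − p). The sample size section gives n = 50 per group planned and 164 / 4 = 41 evaluable. The rejection rate at the nominal 5% level is:

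| h (SD) | n per group | dp = 0 | dp = 0.2 | dp = 0.4 | dp = 0.6 |
|---|---|---|---|---|---|
| 0.25 | 41 | 5.0% | 5.6% | 7.4% | 10.8% |
| 0.25 | 50 | 5.0% | 5.7% | 8.0% | 12.2% |
| 0.5 | 41 | 5.0% | 7.3% | 15.5% | 31.4% |
| 0.5 | 50 | 5.0% | 7.9% | 18.2% | 37.9% |
| 1.0 | 41 | 5.0% | 14.0% | 46.7% | 85.4% |
| 1.0 | 50 | 5.0% | 16.3% | 55.7% | 92.1% |

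The range runs from negligible to severe, and nothing in the article locates the trial within it. The dp = 0 column shows that a common position at each visit removes the between-group artefact entirely.

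**The case against.** The strongest objection concerns the comparison between groups. A reader might infer that the earlier-training groups will be seated sooner and so will be measured as weaker. The article does not say this. Early and late stage can be read simply as time since surgery, which is the same for all groups. The outcome assessor is blinded, so position cannot be chosen by known allocation, although the patient's condition could still influence it. The schedule also limits the exposure. Resistance training starts in week 3 or week 4 depending on group, so that contrast can show mainly at weeks 6 and 9, when a common sitting position is most plausible. The starts of phase 2 differ only between day 3 and 1 week. All of this stands, and it reduces the between-group effect to a possibility.

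It can also be said that a journal article need not list test positions by visit. That is fair for a detail left out. Here, however, the article states a rule, and the rule is that the position changes. The trend is affected whichever visit the full protocol may name for the switch.

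Thirdly, the offset presupposes a dynamometer reading not zeroed or corrected for limb weight, on which the article is silent. The figures in newtons do not apply to manual muscle test grades. Both conditions are accepted. With a gradual change, the effect on a group mean is also a spread-out flattening of the trend, not a visible drop at one visit.

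Finally, a reader might extend the point to the primary outcome, since the Constant-Murley Score contains a strength item. The article does not state the test position for that item, so it gives no ground for doing so.

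**Conclusion.** The concern holds in a limited form, for one secondary outcome. The strength series from day 3 to week 9 changes its test position by design, so the planned repeated-measures reading of strength as recovery mixes two things. This follows from the text, provided that readings are not corrected for limb weight. Under the assumed limb mass and lever ratio, the offset is about 10 to 20 N.

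Distortion between groups at a given visit is possible because no common switch visit is fixed. It requires the seated share to differ between groups, which the article neither states nor rules out. Its size cannot be derived from the document; the rejection rates above show only what would follow from assumed values. The primary analysis is not called into question.

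**What to change.** For the strength outcome, state one test position and use it at every outcome visit in all four groups. This looks workable, since the same section already fixes a single position for each range-of-motion measure. The investigators should choose the position.

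If one position is not workable early after surgery, name one visit at which every patient switches, regardless of group or progress. Record the position at each test, and do not analyse force as a trend across the switch. Testing both positions at the switch visit is optional; it would let the offset be estimated.

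The Trial status section shows that patients have already been recruited. For those already assessed, report test position by group and visit where it was recorded, and interpret the strength results accordingly.

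The cost is protocol wording and an instruction to assessors, plus a second short test at one visit if that option is taken. The small downside is that a single position may suit some patients less well.

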### Training sessions

First, all patients will undergo preoperative assessment and rehabilitation education, including investigation of the patient’s basic information, medical history, and therapeutic schedule, and they will be taught how to undergo rehabilitation. Patients will be taught according to the special BC Rehabilitation Mission Manual to strengthen their understanding regarding the importance of postoperative rehabilitation of BC and to increase their compliance.

The exercise program will be divided into four phases. Phase 1 will consist of the following four movements: (1) The isometric handgrip exercise will be adapted for 2 min of 5-s contraction and 5-s rest-pause intermittently per set, 3 sets per day. (2) The isotonic contraction exercises of the wrist and elbow will not be loaded. Full range of joint motion will be performed, 10–15 times per set in each direction, 3 sets per day. (3) Isometric contraction of the shoulder joint will be performed in both the flexion and abduction directions. Muscles will be allowed to contract for 10 s and rest for 5 s, 10–15 times per set in each direction, 3 sets per day.

Phase 2 will be the isotonic contraction of the shoulder joint in both flexion and abduction. According to the pre-training assessment results, researchers will adjust the appropriate ROM for patients with gravity as the load, 10–15 times per set in each direction, 3 sets per day.

Phase 3 will involve active stretching of the shoulder flexion and abduction. The patient will be asked to face or side face the wall, place her hand on the wall, and slowly crawl her fingers upward. When the patient feels that the armpit has a slight pulling or pain, she will be asked to stop moving her fingers, stretch the shoulder joint for 20–30 s, and then slowly move the arm away from the wall. The same movement will be repeated 10–15 times per set, 3 sets per day.

Phase 4 will involve PRT of shoulder flexion and abduction. Based on the ROM and muscle strength results of the pre-training assessment, the researchers will adjust the appropriate resistance to allow the patients to lift repetitively for 8–15 times per set, 3 sets per day. Providing resistance can be achieved through equipment, such as elastic bands and barbells.

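### Shoulder strength is read in both arms but compared by ANOVA with no covariate and no stated arm; an early unoperated-arm reading could recover precision at almost no cost

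*Protocol article*

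**What the plan says.** All of this is in the protocol article.

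- **Measurement (Assessment for training).** Strength is taken as three maximal contractions per direction, "recording the highest data from three attempts", and "Each arm will be measured separately". Manual muscle testing and a dynamometer are both named. Patients are tested supine early and seated later.
- **Circumference (same section).** Here the opposite limb has an explicit role: "the circumferences of the bilateral arms in a specific position will be measured, and the differences will be compared between the two sides". No side difference, ratio or reference arm is defined for strength.
- **Early readings (same section).** The six training measurements, muscle strength among them, are taken on postoperative day 1, day 3 and at 1 week.
- **Outcome schedule (Secondary parameters).** "Shoulder ROM and strength will be assessed at postoperative 3 days and 1, 2, 3, 6, and 9 weeks". On method: "Assessment methods and principles are the same as those for pre-assessments".
- **Before surgery (Training sessions).** "all patients will undergo preoperative assessment and rehabilitation education, including investigation of the patient’s basic information, medical history, and therapeutic schedule". Strength is not among the listed items.
- **Timelines (Training timelines).** Phase 1 starts on day 1 for everyone. The groups first differ when C and D start phase 2 on day 3.
- **Analysis (Statistical analyses).** One-way ANOVA compares the four groups on CMS and on "EORTC QLQ-BR23, SF-36, ROM, strength, grip, circumference, PDV, and pain". No covariate is named and the arm is not stated. Repeated-measures ANOVA is used to follow recovery over time.

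**The concern.** Women aged 25 to 75 are eligible, so they can be expected to differ in strength for reasons unrelated to the training timeline. A preoperative reading of the same arm would be the usual way to take that variation out, but none is described. The unoperated arm is the nearest substitute that the protocol collects. An ANOVA without a covariate leaves between-woman variation in the error term, and the repeated-measures analysis, which describes recovery over time, does not give the unoperated arm a role either.

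The sample size was set for CMS alone, so nothing shows that the strength comparison is adequately powered. Strength is also what the phase 4 resistance exercises train directly. What is at stake is the precision of that secondary comparison. A second, smaller matter is that the analysed strength variable is not fully defined, because two arms are read and only the word strength appears in the analysis section.

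**Working it through.** **No plan figure to reproduce.** The Sample size section concerns CMS only (164 patients, raised to 50 per group). It gives no effect size, standard deviation or power for strength.

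**Inputs from the article**
- Four groups, 1:1:1:1, 200 enrolled, 20% loss: 200 × 0.80 = 160 analysed.
- Significance level 0.05.

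**Inputs assumed**
- r, the correlation between the early unoperated-arm reading and operated-arm strength at a later visit: 0.3 to 0.8.
- Effect size f (standard deviation of the group means divided by the within-group standard deviation, unadjusted): 0.20, with 0.25 as a second case.

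**Step 1: error variance.** With one covariate, the residual variance is (1 − r²) times the unadjusted variance, and the equivalent sample multiplier is 1/(1 − r²).

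**Step 2: power.** Noncentral F with 3 numerator degrees of freedom and noncentrality λ = N f²/(1 − r²). Denominator degrees of freedom are 160 − 4 = 156 unadjusted and 155 with the covariate. The critical value is 2.66 in both cases. At f = 0.20, N f² = 160 × 0.04 = 6.4; at f = 0.25 it is 160 × 0.0625 = 10.0.

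| r | 1 − r² | Sample multiplier | λ at f = 0.20 | Power, f = 0.20 | Power, f = 0.25 |
|---|---|---|---|---|---|
| none | 1.00 | 1.00 | 6.40 | 53.6% | 74.9% |
| 0.3 | 0.91 | 1.10 | 7.03 | 58.0% | 79.2% |
| 0.5 | 0.75 | 1.33 | 8.53 | 67.3% | 87.1% |
| 0.7 | 0.51 | 1.96 | 12.55 | 84.8% | 96.9% |
| 0.8 | 0.36 | 2.78 | 17.78 | 95.2% | 99.6% |

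**Step 3: cost if the covariate is useless.** With r = 0, λ stays at 6.4 and one degree of freedom is lost. Power remains 53.6% to one decimal.

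**Step 4: covariate or side-to-side difference.** With equal standard deviations in the two arms and both read at the same visit, a simple difference has variance 2(1 − r) times the raw value: 1.40 at r = 0.3, 1.00 at 0.5, 0.60 at 0.7 and 0.40 at 0.8. A difference therefore loses precision below r = 0.5, whereas the covariate does not at any r (0.91, 0.75, 0.51, 0.36).

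**Step 5: which reading is safe.** The exercises are not said to be confined to the operated side, so a later unoperated-arm reading could carry a training effect, and adjusting for it could remove part of the effect of interest. A day-1 reading precedes any group-specific exercise. A day-3 reading does so only if it is taken before the first phase 2 session in groups C and D, and the article does not fix that order.

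**The case against.** The strongest reply is that nothing here is stated wrongly. Allocation is randomised and concealed, so the unadjusted comparison is valid, and a covariate for one of many secondary outcomes is an efficiency preference. The article condenses a longer protocol, and the derivation of a secondary variable is commonly left to documents not shown. The first part stands: there is no bias. The second stands in part. The arm and form of the variable may well be defined elsewhere, but the article does name the between-group method for strength, and a better one is available from readings already planned.

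Several stronger readings are tempting and are not supported:

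- **That strength is analysed as a raw value.** This is the natural reading, but it is not written.
- **That between-woman variation is large or dominates the error.** The documents give no figure. The relevant r links different arms at different times, up to week 9, with a change of posture from supine to seated, after surgical injury and possibly during chemotherapy. If manual muscle grades are used, an unoperated arm may show little spread. Each of these could lower r; at r = 0.3 the gain at f = 0.20 is about four percentage points.
- **That day 3 is the first reading.** It is the first outcome reading; the training assessments include strength from day 1.
- **That no preoperative value exists.** None is described. The list of preoperative items is introduced as inclusive, and the design diagram is not shown.
- **That the same applies to ROM and grip.** The sentence on separate arms follows the strength procedure; two-arm readings of ROM or grip are not expressly described.
- **That the third study aim is weakened.** That aim concerns recovery of shoulder function, for which CMS is the instrument, and CMS has its own strength item.

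**Conclusion.** The point holds as a low-cost improvement in precision for a secondary outcome. The article has both arms read, describes no preoperative strength value, and names an unadjusted ANOVA without saying which arm enters it. Adjusting for an unoperated-arm reading taken before the timelines diverge would reduce error variance at any non-zero correlation, for one degree of freedom.

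The size is uncertain. It runs from a 9% reduction in error variance at r = 0.3 to 64% at r = 0.8; in power, from 54% to between 58% and 95% at f = 0.20. These figures rest on assumed r, assumed f, 160 women analysed and a linear relation with equal slopes across groups. They show what could be gained and do not estimate what this trial will gain. A reader might infer that the strength comparison is invalid or the trial's conclusion threatened; neither follows. The primary CMS result is untouched.

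**What to change.** In Statistical analyses, state that operated-arm shoulder strength is the analysed variable. At each later visit compare the four groups by ANCOVA, with the woman's own unoperated-arm strength before the timelines diverge as covariate, matched by direction (flexion, abduction).

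Fix in advance which reading that is: the day-1 training assessment, or the day-3 reading provided it is taken before the first phase 2 session. Record the device and the posture, so that the covariate and the outcome are on known scales. Use the covariate form in preference to a side-to-side difference, which adds variance when the correlation is below 0.5. Extend the approach to ROM or grip only if both arms are in fact read.

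The cost is one degree of freedom, a sentence or two of analysis text and a timing rule for the early reading. If day 1 is chosen, that training reading must also be kept in the trial database. No visit, measurement or treatment changes, and because the data analyst is to be blinded, the change can be made before allocation is revealed.
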